# Adjunctive dexamethasone for the treatment of HIV-uninfected adults with tuberculous meningitis stratified by Leukotriene A4 hydrolase genotype (LAST ACT): Study protocol for a randomised double blind placebo controlled non-inferiority trial

**DOI:** 10.12688/wellcomeopenres.14007.1

**Published:** 2018-03-20

**Keywords:** Tuberculous meningitis, HIV-uninfected, Dexamethasone, Drug induced liver injury, LTA4H, Adrenal suppression, Hyponatraemia

## Abstract

**Background: **Tuberculosis kills more people than any other bacterial infection worldwide. In tuberculous meningitis (TBM), a common functional promoter variant (C/T transition) in the gene encoding leukotriene A4 hydrolase (LTA4H), predicts pre-treatment inflammatory phenotype and response to dexamethasone in HIV-uninfected individuals. The primary aim of this study is to determine whether LTA4H genotype determines benefit or harm from adjunctive dexamethasone in HIV-uninfected Vietnamese adults with TBM. The secondary aim is to investigate alternative management strategies in individuals who develop drug induced liver injury (DILI) that will enable the safe continuation of rifampicin and isoniazid therapy.

**Methods: **We will perform a parallel group, randomised (1:1), double blind, placebo-controlled,  multi-centre Phase III non-inferiority trial, comparing dexamethasone versus placebo for 6-8 weeks in addition to standard anti-tuberculosis treatment in HIV-uninfected patients with TBM stratified by LTA4H genotype. The primary endpoint will be death or new neurological event. The trial will enrol approximately 720 HIV-uninfected adults with a clinical diagnosis of TBM, from two hospitals in Ho Chi Minh City, Vietnam. 640 participants with CC or CT- LTA4H genotype will be randomised to either dexamethasone or placebo, and the remaining TT- genotype participants will be treated with standard-of-care dexamethasone. We will also perform a randomised comparison of three management strategies for anti-tuberculosis DILI. An identical ancillary study will also be perfomed in the linked randomised controlled trial of dexamethasone in HIV-infected adults with TBM (ACT HIV).

**Discussion: **Previous data have shown that LTA4H genotype may be a critical determinant of inflammation and consequently of adjunctive anti-inflammatory treatment response in TBM. We will stratify dexamethasone therapy according to LTA4H genotype in HIV-uninfected adults, which may indicate a role for targeted anti-inflammatory therapy according to variation in LTA4H C/T transition. A comparison of DILI management strategies may allow the safe continuation of rifampicin and isoniazid.

## Introduction

### Background

Tuberculous meningitis (TBM) is the most severe form of tuberculosis, resulting in death or neurological disability in approximately 40% of HIV-uninfected sufferers, and 70% of those co-infected with HIV. Effective anti-tuberculosis chemotherapy has been available for more than 50 years, yet tuberculosis kills more people than any other single bacterial infection worldwide. Diagnosing TBM is difficult and depends upon detecting low numbers of
*M. tuberculosis* bacteria in cerebrospinal fluid (CSF). Rifampicin (R), isoniazid (H), pyrazinamide (Z) and ethambutol (E) are the first-line antibiotics for all forms of drug-susceptible tuberculosis. These agents, used daily and in combination, kill the bacteria and prevent the emergence of resistance. There is concern that the blood-brain barrier reduces the concentrations of anti-tuberculosis drugs in the brain which may attenuate both bacterial killing and clinical response
^1^. The most recent Cochrane meta-analysis and systematic review of adjunctive corticosteroids for TBM
^2^ concluded that corticosteroids likely reduced death from TBM in HIV-uninfected individuals in the short term (up to 18 months of follow-up), but had no clear impact on longer term neurological disability or survival.

### Complications of TBM

Hydrocephalus, stroke, and tuberculoma formation are important and common complications of TBM
^3^, however little evidence exists to guide their optimal management. Drug induced hepatitis associated with anti-tuberculosis treatment occurs in around 10% of HIV-uninfected patients
^4^, and can be attributed to rifampicin, isoniazid or pyrazinamide. Determining which drug is responsible is difficult. Corticosteroid therapy leads to hyperglycaemia, and during treatment of TBM dexamethasone may worsen, or reveal, diabetes. Severe hyponatraemia (low plasma sodium), high temperature and CO
_2_ retention all exacerbate raised intracranial pressure and require active management. The role of corticosteroids in adrenal suppression in TBM requires further investigation.

### The role of LTA4H

How corticosteroids improve survival in HIV-uninfected patients with TBM, and whether they do so in all HIV-uninfected patients, remains uncertain and is the focus of the LAST ACT trial. A common functional promoter variant (C/T transition) in the gene encoding LTA4H, which determines the balance of pro- and anti-inflammatory eicosanoids, appears to predict pre-treatment inflammatory phenotype and response to dexamethasone in HIV-uninfected participants
^5,
6^. In humans, LTA4H rs17525495 allele homozygosity (TT and CC respectively) was associated with susceptibility to mycobacterial infection, albeit with opposite inflammatory states - high for the TT-genotype and low for the CC-genotype
^5^. Heterozygotes (CT) had an intermediate inflammatory response, and were more likely to survive TBM
^5^. A retrospective study, analysing HIV-uninfected Vietnamese adults with TBM enrolled into an earlier randomised controlled trial of adjunctive dexamethasone
^7^ and prospective TBM observational studies, found that the survival benefit of dexamethasone was restricted to the hyper-inflammatory LTA4H TT-genotype patients, with possible harm suggested in hypo-inflammatory CC-genotype patients
^5^. This suggests LTA4H genotype may be a critical determinant of inflammation and consequently of adjunctive anti-inflammatory treatment response.

### Hypotheses

Dexamethasone has been shown to improve survival in HIV-uninfected individuals with TBM
^2^. Previous data strongly suggests hyperinflammatory LTA4H TT-genotype patients with TBM benefit from dexamethasone, and that adjunctive dexamethasone may not benefit, and may cause harm, when given to patients with LTA4H CT or CC-genotype.
**Our primary hypothesis is that dexamethasone has no benefit in patients with CC or CT genotype for adults with TBM**. We regard the benefit of dexamethasone in patients with LTA4H TT-genotype as established and will hence not randomise them. In contrast, patients with CT or CC-genotypes will be randomised in a practice-defining randomised controlled trial (RCT) to assess whether placebo is non-inferior or even superior to dexamethasone in these patients. Our secondary hypothesis is that current guidelines for the management of anti-tuberculosis DILI in those with TBM result in the premature cessation of rifampicin and isoniazid (the critical active drugs in early therapy) and place patients at unnecessary risk of TBM-related death and disability.

## Study aims

### Primary aim

Our primary aim is to determine whether LTA4H genotype, defined at randomisation, determines dexamethasone’s clinical effectiveness when added to the first 6–8 weeks of anti-tuberculosis treatment of TBM with dexamethasone duration depending on Medical Research Council (MRC) grade (
Supplementary File 1) at the start of treatment. In making this assessment we not only determine whether in LTA4H CT or CC-genotype patients placebo is non-inferior to dexamethasone with respect to survival and the incidence of new neurological events, but also with respect to disability assessed by the modified Rankin scale (
Table 1), the frequency of severe and serious adverse events, and the need for rescue corticosteroids.

**Table 1. T1:** Modified Rankin scale.

Score	Description
0	No symptoms
1	Minor symptoms not interfering with lifestyle
2	Symptoms that lead to some restriction in lifestyle, but do not interfere with the patients ability to look after themselves
3	Symptoms that restrict lifestyle and prevent totally independent living
4	Symptoms that clearly prevent independent living, although the patient does not need constant care and attention
5	Totally dependent, requiring constant help day and night
6	Death

### Secondary aims

Our secondary aim is to investigate alternative management strategies in a subset of patients who develop DILI that will enable the safe continuation of rifampicin and isoniazid therapy whenever possible.

### Design and setting

LAST ACT is a parallel group, randomised (1:1), double blind, placebo-controlled, multi-centre Phase III non-inferiority trial, comparing dexamethasone versus placebo for 6-8 weeks in addition to standard anti-tuberculosis treatment in HIV-uninfected patients with TBM stratified by LTA4H genotype.
** The trial will be set in two hospitals in Ho Chi Minh City, Vietnam. The trial will enrol approximately 720 HIV-uninfected adults (≥18 years) with a clinical diagnosis of TBM, as judged by the attending physician, requiring immediate anti-tuberculosis treatment. Amongst these, 640 participants with CT or CC- LTA4H genotype will be randomised to either dexamethasone or placebo. The remaining participants (approximately 80) with TT-genotype will be treated with standard-of-care dexamethasone. The trial schema is shown in
Figure 1.

**Figure 1. f1:**
[figure not shown]
Trial Schema for LAST ACT trial (main trial).

An ancillary DILI strategy study will perform a randomised comparison of management strategies in DILI early in anti-tuberculosis treatment (the intensive phase). We will perform an open, randomised comparison of three management strategies with the aim of demonstrating which strategy results in the least interruption in rifampicin and isoniazid treatment. All patients enrolled in the main trial will be eligible to take part in this study, with the exception of those known to have TBM caused by isoniazid resistant or MDR
*M. tuberculosis*. An identical ancillary study will also be performed in the linked RCT of dexamethasone in HIV-infected adults with TBM (ACT HIV)
^8^. The results from both trials will be reported together, after the primary results from both trials have been published. This trial schema is shown in
Figure 2.

**Figure 2. f2:**
[figure not shown]
Trial Schema for DILI strategy study.

### Ancillary studies

Seven ancillary studies will be conducted within the trial. The studies are as follows:

**Ancillary study 1:** A randomised comparison of management strategies in response to DILI (as above). (All patients.)
**Ancillary study 2:** Host and bacterial genetic determinants of treatment response. We hypothesise that the LTA4H gene, and genes involved in related inflammatory pathways, may influence participant inflammatory state, TBM severity, and treatment response. We will also examine genetic variants associated with the development of DILI. (All patients.)
**Ancillary study 3:** Impact of dexamethasone on CSF inflammation and gross cerebral pathology (assessed by serial brain MRI). We will investigate how dexamethasone influences the resolution of inflammatory markers in the CSF and the gross pathological consequences of TBM on the brain (hydrocephalus, stroke, and tuberculoma formation). (Hospital for Tropical Diseases (HTD) patients only.)
**Ancillary study 4:** Influence of diabetes mellitus on presentation and response to treatment. We will investigate whether diabetes mellitus influences clinical presentation and CSF inflammatory phenotype (linking with ancillary study 2), and how it impacts upon treatment outcomes. (All patients)
**Ancillary study 5:** Influence of Strongyloides infection on presentation and response to treatment. We will determine whether Strongyloides co-infection alters clinical and/or CSF inflammatory phenotype at TBM presentation (linking with ancillary study 2) and treatment response. (All patients.)
**Ancillary study 6:** Pathophysiology and treatment of hyponatraemia and raised intracranial pressure. We will investigate the pathophysiology of TBM-associated hyponatraemia, enabling a better understanding of the causes of hyponatraemia, the relationship between plasma sodium and elevated intracranial pressure, and the best management of severe hyponatraemia. (HTD patients only.)
**Ancillary study 7:** Dexamethasone induced adrenal suppression. We will investigate whether the use of corticosteroids in the doses prescribed in infectious diseases is associated with significant adrenal suppression. (HTD patients only.)

## Endpoints

### Primary endpoint – main trial

The primary endpoint is death or new neurological event (defined as a fall in Glasgow coma score (GCS) by ≥2 points for ≥2 days from the highest previously recorded GCS (including baseline) or the onset of any of the following clinical adverse events: cerebellar symptoms, focal neurological signs, or new seizures) during 12 months from randomisation. Survivors without a new neurological event known to be alive at 12 months will be censored at that time-point and subjects who withdrew or were lost to follow-up before 12 months will be censored at the date they were last known to be alive.

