### Secondary endpoints – main trial

The secondary endpoints of the main trial are as follows:

a)Overall survival during a follow-up period of 12 months. Overall survival is defined as the time from randomisation to death, during a follow-up period of 12 months. Survivors known to be alive at 12 months will be censored at that time-point and subjects who withdrew or were lost to follow-up before 12 months will be censored at the date they were last known to be alive.b)Neurological disability at 12 months. Disability will be assessed by the modified Rankin scale (
Table 1) on days 30 and 60 from randomisation, and then monthly until the end of anti-tuberculosis drugs. The main endpoint is the 12-month assessment and subjects who died before 12 months will be treated as having a score of 6 (‘Dead’).c)Severe (grade 3&4) and serious adverse events. Comparison of the frequency of severe and serious adverse events between treatment groups will form an important part of the study analysis.d)Requirement for ‘rescue’ corticosteroids. Neurological complications occurring after the start of anti-tuberculosis chemotherapy for TBM are common. The cause varies, but includes hydrocephalus, infarcts, tuberculoma formation and hyponatraemia. If the symptoms are thought to be caused by tuberculomas, doctors may re-start or increase the dose of corticosteroids. In this trial, any re-start or dose increase of corticosteroids during the 12-month follow-up will be defined as ’rescue’ corticosteroids.

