### Inpatient assessment

GCS and new focal neurology will be recorded daily during the participant’s hospital admission. Participants will be visited by one of the research team at screening, baseline, randomisation (when LTA4H genotype returns), and at least every 3 days for the first 4 weeks of treatment (unless they are discharged or die before 4 weeks) and then at least every 7 days whilst they remain in hospital. Formal trial clinical assessments will occur on day 0, 3, 7, 10, 14, and weekly thereafter until discharge (+/- 1 day).

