### Outpatient assessment

After discharge clinical assessments will occur monthly until 12 months. Some of these assessments can be made by phone. Formal outpatient review will occur monthly (+/- 7 days) for at least the first 2 months following hospital discharge. The patient should have formal outpatient review at least every 2 months until month 12 after randomisation. The endpoints of survival and neurological disability by 12 months (-0/+1 month) should be assessed by formal outpatient review whenever possible.

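### The composite primary endpoint takes its censoring date from overall survival, so time in which only survival is known counts as free of neurological events

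*Protocol article*

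**What the plan says.** The section on the primary endpoint of the main trial combines death with a new neurological event. The neurological part is a "fall in Glasgow coma score (GCS) by ≥2 points for ≥2 days from the highest previously recorded GCS" or the onset of cerebellar symptoms, focal signs or seizures. For patients without full follow-up, "subjects who withdrew or were lost to follow-up before 12 months will be censored at the date they were last known to be alive". For those who reach the end, "Survivors without a new neurological event known to be alive at 12 months will be censored at that time-point".

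Item (a) of the secondary endpoints, overall survival, has the same clause for lost and withdrawn patients. Its end-of-study clause is "Survivors known to be alive at 12 months will be censored at that time-point", which differs from the primary endpoint only in dropping the condition on neurological events. The section on the primary endpoint analysis restates the endpoint for the Cox model and gives no other censoring date. Nothing in the article ties censoring to the last neurological assessment.

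On ascertainment, "GCS and new focal neurology will be recorded daily during the participant’s hospital admission". Later, "After discharge clinical assessments will occur monthly until 12 months", and "Some of these assessments can be made by phone". In-person review is required at least every two months. Missed visits lead to up to three calls and then up to three home visits (Recruitment and retention). A participant who withdraws on regaining capacity has no further trial procedures (Consent), though participants may later re-consent (Withdrawing from the trial).

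**The concern.** Being alive settles one component of the composite and is silent on the other. A last-known-alive date fits overall survival because survival is all that the endpoint asks about. In the composite, a patient whose neurological status was last ascertained at month 3 and who was last known alive at month 9 adds six event-free months to the risk set, although only a death could have been recorded in them. The end-of-study clause has a milder form of the same weakness: it asks for no recorded neurological event and for proof of life at 12 months, but not that neurological status was followed to that date.

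At stake are the 12-month event risks, the Kaplan-Meier estimates at 3, 6, 9 and 12 months and, if ascertainment gaps differ by arm, the hazard ratio on which non-inferiority is judged.

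**Working it through.** **1. The plan's own figures.** The sample size section gives a margin HR of 0.75 and an assumed HR of 1.15 (dexamethasone vs placebo), one-sided 2%, 80% power, 35% risk on dexamethasone, overall risk of at least 32%, and an 11% inflation.

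- Events = 4(z0.98 + z0.80)² / [ln(1.15/0.75)]² = 4(2.0537 + 0.8416)² / 0.4274² = 183.5, so 184 as stated.
- Patients = 184/0.32 = 575; 575 × 1.11 = 638, stated as 640.
- Placebo risk = 1 − 0.65^(1/1.15) = 31.2%, as stated.

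The point does not dispute these figures, and the fix does not change them.

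**2. Uncounted neurological events.** The documents do not give the inputs, so these are assumptions: share of patients with a gap L = 2 to 10%; gap g = 1 to 6 months; neurological share of the event hazard f = 30 to 70%; constant hazards. The pooled 12-month risk is (35% + 31.2%)/2 = 33.1%, so h = −ln(1 − 0.331)/12 = 0.0335 per month.

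Uncounted events = 640 × L × [1 − exp(−f·h·g)]

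| L | g (months) | f | Uncounted events |
|---|---|---|---|
| 2% | 1 | 30% | 12.8 × 0.0100 = 0.1 |
| 5% | 3 | 50% | 32 × 0.0490 = 1.6 |
| 10% | 6 | 70% | 64 × 0.1313 = 8.4 |

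The largest case is 8.4/640 = 1.3 percentage points of 12-month risk, as a rough upper figure.

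**3. Power.** Power = Φ[(√d/2) × 0.4274 − 2.0537]. With d = 184 it is 80.1%; with d = 184 − 8.4 = 175.6 it is 78.2%.

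**4. Hazard ratio at the margin.** The monthly hazard is 0.0359 on dexamethasone (−ln 0.65/12) and 0.0359/0.75 = 0.0479 on placebo. In an affected arm, 90% of patients are fully followed for 12 months. The other 10% are fully observed for 3 months and then contribute g months in which only deaths, at hazard (1 − f)h, are recorded. The apparent rate is expected events divided by expected person-months.

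Worked case, f = 70% and g = 6, per patient randomised:
- Placebo with gap: 0.4138/8.993 = 0.0460.
- Dexamethasone with gap: 0.3308/9.581 = 0.0345.

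| f | g (months) | Gap in placebo only | Gap in dexamethasone only | Gap in both |
|---|---|---|---|---|
| 50% | 3 | 0.761 | 0.739 | 0.750 |
| 50% | 6 | 0.771 | 0.730 | 0.750 |
| 70% | 3 | 0.766 | 0.735 | 0.750 |
| 70% | 6 | 0.0359/0.0460 = 0.780 | 0.0345/0.0479 = 0.721 | 0.751 |

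For scale, the standard error of the log HR at 184 events is 2/√184 = 0.147. The largest shift towards non-inferiority, ln(0.780/0.75) = 0.039, is 0.27 standard errors.

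**The case against.** The strongest reply is that the protocol's own contacts cover most of the time in question. The monthly assessments after discharge are clinical assessments even when made by phone, and the Clinical assessment section includes conscious level, new focal deficit and serious adverse events. Seizures and new deficits can be reported afterwards with an onset date. Home visits are not limited to vital status, and no registry or passive tracing is described. For most lost patients, then, the last proof of life and the last neurological information should fall on or near the same date. This stands, and it limits the size of the problem. It does not cure the rule, because the text does not require the two dates to agree. A sustained fall in GCS is also the component hardest to establish by phone or in retrospect.

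Three stronger readings are tempting and are not supported:

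- A reader might infer that missed events pull this trial towards non-inferiority. For a hazard ratio, equal gaps leave the estimate essentially unchanged (last column above). Unequal gaps can move it either way, and the documents give no reason to expect unequal gaps in a double-blind trial.
- A reader might infer that the 12-month clause ignores neurological events. It does require that none has occurred; what it omits is a requirement that neurological status was ascertained to that date.
- A reader might extend the point to secondary endpoint (c) of the DILI strategy study. That item states no censoring rule, so no fault is shown there.

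**Conclusion.** The point holds as a mismatch between a stated rule and its endpoint: the last-known-alive date is right for overall survival and wrong for the neurological part of the composite. It matters only where survival is known later than neurological status.

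The sure consequence is that absolute event risks are understated in such patients. Under the assumed ranges this is about 0 to 8 events among 640 patients. Bias in the hazard ratio needs gaps that differ by arm. With a gap in 10% of one arm only, starting at month 3, a true 0.75 reads as about 0.76 to 0.78 (gap on placebo) or 0.72 to 0.74 (gap on dexamethasone). All of this rests on assumed loss, gap length and neurological share, with constant hazards. Severity is minor to moderate: the expected shift is small, but it concerns the primary endpoint of a non-inferiority trial and is easily put right.

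**What to change.** In the primary endpoint definition:

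1. Censor event-free patients not known to have died at the last contact at which both vital and neurological status were ascertained, capped at 12 months. State that a phone clinical assessment counts if it asks about neurological events. Apply the same condition to 12-month survivors.
2. Keep every known death within 12 months as a primary event. Simply censoring at the last neurological assessment would discard observed deaths in patients who are plausibly sicker.
3. Prespecify how a death after a long neurological gap is counted, because counting late deaths while censoring survivors early can itself bias the estimate. Add a sensitivity analysis that censors such deaths at the last neurological assessment.
4. Keep last-known-alive censoring for overall survival, and as a sensitivity analysis of the composite.

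The cost is a few sentences, slightly less counted follow-up time and a little more analysis work. It relies on the date and content of each contact being recorded; the case report form is not shown, so that should be confirmed. The 184 events and 640 patients stay as they are.
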